## Abstract

**Background:**

Many patients with metastatic breast cancer can live relatively long lives but are challenged by treatment- and cancer-related side effects such as weight gain, physical deconditioning, and reduced quality of life, possibly affecting survival. In particular, endocrine treatments are associated with an increased risk of weight gain and adverse metabolic effects. There is a need for interventions to prevent side effects among patients with disseminated breast cancer. Exercise is found to be effective in improving quality of life, metabolic health, and body composition in the curative setting, yet evidence in the metastatic setting is sparse. The aim of this study is to assess feasibility of a 12-week exercise intervention for metastatic breast cancer patients with overweight receiving endocrine therapy and to explore potential effects on metabolic health, body composition, physical performance, obesity-related biomarkers, and patient-reported outcomes.

**Methods:**

The FEMA study is a randomized controlled feasibility trial in which 21 endocrine-treated patients with metastatic breast cancer and overweight will be randomly assigned in a 2:1 ratio to either a 12-week training program with three weekly training sessions (intervention), or usual care (control), which includes standard clinical follow-up and supportive care without structured exercise. Feasibility will be assessed based on recruitment rate, adherence, retention, and acceptability, employing both quantitative and qualitative approaches for data collection. Participants’ experiences will be explored by interviews and analyzed based on content analysis. Data are collected from blood samples, bioelectrical impedance analysis, physical performance tests, blood pressure measurements, and validated questionnaires on health-related quality of life, self-efficacy for coping with cancer, and sleep quality for explorative analyses.

**Discussion:**

The planned study will allow us to determine whether this 12-week exercise intervention is feasible in endocrine-treated metastatic breast cancer patients with overweight and explore potential effects on metabolic health, body composition, physical performance, obesity-related biomarkers, and patient-reported outcomes. Information from feasibility outcomes will inform the design of a future definitive randomized controlled trial.

**Trial registration:**

Retrospectively registered on March 6, 2024, at ClinicalTrials.gov (NCT06343987).

**Supplementary Information:**

The online version contains supplementary material available at 10.1186/s40814-025-01621-9.

## Background

A substantial increase in the prevalence of overweight and obesity globally is also reflected in Scandinavia, including Denmark [1]. According to the Danish Health Authority, 53% of the Danish adult population have a body-mass index (BMI) ≥ 25 kg/m^2^ and are, by definition, overweight, whereas 18.5% have a BMI ≥ 30 kg/m^2^ and are considered to have obesity [2]. Overweight presents a significant individual and public health challenge, as excess weight is associated with an increased risk of many health issues, including type 2 diabetes, cardiovascular diseases, and several types of cancers [3–6]. In the case of breast cancer (BC), which is the most common cancer in women worldwide [7], accounting for approximately 2.3 million new cases in 2022 [8], overweight is not only associated with an increased risk of developing BC but also with a less favorable prognosis [9–11]. At diagnosis, women with overweight are more likely to have more advanced BC [12] and face an elevated risk of developing distant metastases compared to BC patients with normal weight [9].

Several factors may explain the inferior prognosis observed among BC patients with overweight. Women who are overweight tend to have higher insulin levels, systemic low-grade inflammation, and, in postmenopausal women, higher circulating levels of estrogen [13, 14]. Hyperinsulinemia and chronic low-grade inflammation possibly contribute to more aggressive BC and promote tumor progression [15, 16]. Additionally, systemic cancer treatments, e.g., chemotherapy and endocrine-based therapy, may be less effective in BC patients with overweight [17, 18], altogether increasing the risk of the cancer metastasizing.

For women with metastatic breast cancer (MBC), improved cancer care is a high priority [19]. Despite having an incurable disease, many patients can live relatively long lives after diagnosis, with a median overall survival of 57 months for patients with estrogen receptor-positive (ER +) MBC [20]. However, patients with MBC often experience significant cancer- and treatment-related side effects, such as metabolic disruption and weight gain, possibly related to endocrine treatment [21, 22], fatigue, depression, and physical deconditioning, adversely affecting their health-related quality of life (HRQoL) [23–26]. Impaired HRQoL may lead to treatment adjustment or discontinuation, which can affect survival negatively [27].

One potential avenue to combat these adverse outcomes in patients with MBC is through exercise. In recent international guidelines, exercise is recommended in the curative setting alongside and after conventional treatments to reduce side effects and improve survival [28, 29]. However, no recommendations are provided in the metastatic setting, as evidence of the beneficial effects of exercise in these patients is scarce. While multiple prospective studies have investigated exercise interventions in the curative BC setting, patients with MBC are often not included, even though exercise is found to be safe [30], including for those with bone metastases [31].

A few studies have investigated the effects of exercise in the MBC setting with inconsistent results. In the PREFERABLE-EFFECT study by Hiensch et al. [32], 357 patients were randomized to a 9-month supervised exercise program versus usual care. While exercise was found to significantly improve HRQoL and fatigue, the authors did not examine outcomes on body composition and metabolic health. Scott et al. [33] randomized 65 patients with MBC in treatment with chemotherapy to a 12-week aerobic training program versus a stretching control group. Aerobic training was found to be safe, however not feasible, as almost one-third (N = 9/33) in the intervention group discontinued due to disease progression, lack of motivation or pain.

In a pilot trial, Sheean et al. [34] investigated a 12-week exercise and nutritional intervention versus a wait-list control condition in patients with MBC (*N* = 40), providing lifestyle coaching and intervention support for home-based training. The intervention was deemed feasible and safe and resulted in improvements in HRQoL, fatigue, endocrine symptoms, and visceral fat mass. Results from a full-scale study have yet to be published.

Ligibel et al. [35] conducted a 16-week randomized study of partially supervised aerobic training versus usual care in 101 patients with MBC. The exercise group showed no significant improvements in physical activity or HRQoL. However, a post hoc analysis revealed that patients on endocrine therapy had better cardiorespiratory fitness outcomes and lower dropout rates. The authors concluded that the study’s heterogeneous population, with women at different treatment stages and therapies, led to variations in physical activity and functional outcomes, reducing the power to detect changes. Therefore, they suggest that future studies should focus on more homogenous groups of MBC patients, particularly those on endocrine therapy.

A subgroup of patients with MBC for whom exercise could be particularly beneficial are those who receive endocrine treatment and have overweight or obesity. As seen in Ligibel et al., exercise may be more feasible for those MBC patients who receive endocrine treatment than those receiving chemotherapy. Furthermore, in this patient population, there is a considerable need to mitigate treatment-, cancer- and obesity-related adverse effects on HRQoL, metabolic health, and body composition and to potentially improve survival. In the curative setting, one study investigated a 16-week combined aerobic and resistance exercise intervention in BC survivors with overweight receiving endocrine therapy (*N* = 100). They found significant improvements in metabolic syndrome, sarcopenic obesity, physical fitness, and HRQoL [36, 37]. This needs to be tested in the advanced setting as well.

In this context, we hypothesize that a supervised exercise program is feasible and can improve metabolic health, body composition, and patient-reported outcomes in patients with MBC and overweight treated with endocrine therapy, ultimately improving cancer care in the advanced setting. Therefore, we aim to (1) assess the feasibility of a 12-week PA program for women with MBC and overweight receiving endocrine-based treatment in terms of recruitment rate, adherence, retention, and acceptability and (2) investigate the potential effects of the exercise program on metabolic health, body composition, physical performance, obesity-related biomarkers and patient-reported outcomes such as HRQoL, cancer-related self-efficacy, and sleep quality.

## Method

The present protocol is based on the Standard Protocol Items: Recommendations for Interventional Trials (SPIRIT) [38, 39] and the Consolidated Standards of Reporting Trials (CONSORT) statement extension to randomized pilot and feasibility trials [40], following the editorial guide from Thabane and Lancaster [41]. A SPIRIT flow diagram is provided in Fig. 1, and the SPIRIT checklist can be found in the additional material (Additional File 1).

**Fig. 1 Fig1:**
[figure not shown]
SPIRIT-flow diagram: schedule of enrollment, intervention, and assessment Notes: EORTC-QLQ-C30, The European Organization for Research and Treatment of Cancer QLQ-C30; CBI-12, Cancer Behavior Inventory 12; PSQI, Pittsburg Sleep Quality Index; ISI, Insomnia Severity Index; CSD, Consensus Sleep Diary

### Study design

The FEMA study (Feasibility of Exercise in patients with Metastatic Breast Cancer and Adiposity) is a parallel-group, randomized controlled, feasibility trial with two arms. After providing informed consent, eligible participants are randomly assigned in a 2:1 ratio to the interventional arm, consisting of usual care plus a 12-week exercise program or a usual care-only control arm. Outcome measures are collected at study inclusion (baseline), mid-intervention (6 weeks), post-intervention (12 weeks), and at a 12-week follow-up after the intervention concludes (24 weeks) The study design and timeline are illustrated in Fig. 2 further below.

**Fig. 2 Fig2:**
[figure not shown]
Study design

### Participants and setting

The target population for this study is patients with MBC who are overweight or obese (BMI ≥ 25) and who receive first-line endocrine treatment. We will recruit participants (*N* = 21, see “ Sample size” section below) from the breast cancer outpatient clinic at the Department of Oncology, Aarhus University Hospital, Denmark. The training facilities for the exercise program are provided by the Steno Diabetes Center Aarhus, located at Aarhus University Hospital.

### Eligibility criteria

Patients are eligible for inclusion if they meet the following criteria: (1) diagnosed with MBC; (2) in active first-line endocrine treatment; (3) BMI of 25 kg/m^2^ or higher; and (4) performance status of Eastern Cooperative Oncology Group (ECOG) of 0–1. Participants are excluded according to the following criteria: (1) pregnancy; (2) physical health condition making it either unsafe to participate or preventing them from full participation in the exercise program; and (3) insufficient Danish language skills.

### Recruitment

Project personnel will screen the outpatient BC clinic’s appointment list daily to identify potentially eligible participants. Eligible participants are highlighted in the list to make the attending physician or nurse aware of eligibility. The attending physician or nurse is responsible for informing the patient about the study. If the patient is interested, project personnel will provide detailed information about the study procedures and answer any questions. Eligible participants receive a study information sheet describing the study objectives and methods in detail. The patient is then offered time to consider participation, and a follow-up meeting is scheduled. All participants must provide written consent before participating in any study-related procedures. Those who opt not to participate will be documented in a screening log stored on an internal server. All participants will be compensated for parking or public transportation costs related to study participation.

### Randomization

Recruited participants undergo non-stratified, simple randomization in a 2:1 ratio to either intervention or usual care. The randomization sequence is computer-generated independently through an algorithm used by the Clinical Trial Unit at Aarhus University. When the participants have been randomized, their allocation will be locked in the Research Electronic Data Capture (REDCap) software [42, 43]. The randomization process is not blinded for researchers or participants, as it is not compatible with the study design. Randomization allocation is delivered orally to participants.

### Sample size

As this study is a feasibility trial, no formal sample size calculation was performed, which aligns with published recommendations [40, 41, 44]. The chosen sample size of 21 participants was based on practical considerations, including recruitment potential, funding constraints, and the high level of participant engagement required for an exercise intervention in this patient population. This decision was also informed by previous feasibility studies investigating exercise interventions in cancer populations with similar feasibility outcomes [45–48]. Recommendations for pilot trials typically suggest a sample size of 10 to 40 participants per group [49–51]. Our 2:1 randomization design (14 interventions, 7 controls) does not fully align with these recommendations due to practical constraints and the need to prioritize intervention feasibility while still maintaining a control group for study design experience and exploratory comparisons. However, the total sample size of 21 participants is consistent with feasibility study guidelines, which emphasize that smaller sample sizes are appropriate when assessing process-related outcomes rather than effect sizes [44].

In the interest of transparency, we acknowledge the precision limitations of our feasibility estimates. Assuming an 80% retention rate with *N* = 21, the 95% confidence interval ranges from 62 to 98%. This wide interval is an inherent limitation of feasibility studies but does not invalidate the study’s objectives. While retention rates in pilot trials are often used to inform sample size calculations for definitive trials, this is not the objective of our study. Instead, our focus is on determining whether trial procedures are practical and achievable within study context.

### Intervention

The intervention consists of a 12-week exercise program that features three weekly, 2-h training sessions at the Steno Diabetes Centre, Aarhus, facilitated by a physiotherapist experienced in working with cancer patients. The training sessions consist of a joint warm-up session and functional stability exercises (30 min), followed by individual cardiovascular and resistance training (1 h), ending with a joint stretching session (15 min). The cardiovascular training consists of short but high-intensity sessions, aiming for a Borg Rating of Perceived Exertion of 14–20 [52]. The duration of cardiovascular training is increased each week, combined with an increased number of high-intensity intervals, adjusted individually. Progressive resistance training is conducted as circuit training of three sets incorporating both weight machines and floor exercises. The load is gradually increased over time with decreasing repetitions: weeks 1–4 doing 12 repetitions, weeks 5–8 doing 10 repetitions, and weeks 9–12 doing 8 repetitions. The last 15 min of each training session are spent on socializing and evaluating the training. Participants will only be discontinued from the study in the case of the training being assessed as unsafe by study personnel with medical background.

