### Control group

Participants assigned to the control group receive usual care at the Department of Oncology. They will undergo all study measurements at the defined timepoints, similar to the intervention group. For ethical reasons, the participants are informed of the possibility of being referred to training and rehabilitation at municipal service providers through the Department of Oncology. The participants will receive advice regarding training from the physiotherapist during baseline assessments.

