### Feasibility outcomes

Multiple feasibility outcomes are investigated in this study:Recruitment rate, consisting of the proportion of eligible participants who choose to participate in the study.Adherence to the exercise program, measured as the attendance rate.Retention, defined as the percentage of consenting participants in the intervention and control group completing T3.Acceptability, defined as the participants’ satisfaction with the study and intervention, employing both quantitative (ad hoc questions using Likert-scale scoring and open-ended questions) and qualitative (semi-structured interviews) methods.Adherence to other study procedures, i.e., the rate of completed questionnaires and collected biomarker samples.

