### Progression criteria

To ensure that the feasibility objectives in this study are met, progression criteria for each objective are developed [74]. Defining progression criteria is necessary in the interpretation of trial findings. For this purpose, a traffic light system is employed. In this system, a lower (red) threshold indicates major problems that require urgent attention (and perhaps are unfixable), amber indicates minor problems that require attention, and green indicates areas of no concern [74]. As estimates of rates in the feasibility measures are subject to uncertainty, this system allows for chance variation in contrast to definitive thresholds. We will identify fundamental feasibility measures to accurately weigh the importance of each outcome in the assessment. In Table 1, the progression criteria for each outcome are outlined. These criteria are based on relevant studies, as referenced in the background section, and informed by prior research on feasibility outcomes in exercise interventions for breast cancer populations. To provide an overall assessment of the feasibility of the study, we employ a holistic approach, using quantitative measurements of the progression criteria, data from the evaluation questionnaire, and data on feasibility from the qualitative interviews collectively.

**Table 1 Tab1:** Progression criteria for feasibility objectives

Feasibility objective	Red Major problem	Amber Minor problem	Green No concern	Fundamental objective
Recruitment rate	< 25%	25–33%	≥ 33%	Yes
Attendance rate	< 70%	70–80%	≥ 80%	Yes
Retention rate	< 65%	65–80%	≥ 80%	Yes
Acceptability of intervention^a^	< 75%	75–90%	≥ 90%	Yes
Adherence to other study procedures	< 80%	80–90%	≥ 90%	No

Lower and upper threshold values in the traffic light system for feasibility outcomes

^a^Percentage of participants in the intervention group that answers “Yes” to the question: “Would you recommend others to participate in the physical activity program?” in the evaluation questionnaire

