### Statistical analysis plan

Data are entered into a REDCap database in real time using electronic case report forms.

Baseline data on participant demographics and characteristics will be presented in a descriptive table in accordance with the CONSORT guidelines [43]. For feasibility outcomes, the analysis will be mainly descriptive and focus on confidence interval estimation and not formal hypothesis testing, in accordance with the CONSORT extension to randomized feasibility and pilot trials [40].

The results of the effect measurements will be presented as means, standard deviations, and effect sizes (standardized mean differences) to assess potential effects, but no formal statistical tests will be performed. Effects will be analyzed at T3 (post-intervention), and further analysis will be made to see if these effects sustain until T4 (12-week follow-up post intervention). The semi-constructed interviews will be digitally recorded, transcribed, and analyzed using thematic analysis [78]. Statistical analyses will be carried out using the Stata 18 software [79].

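### The safety rule ends study participation, not only training, so it causes loss of follow-up that can arise in the exercise arm alone

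*Protocol article*

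**What the plan says.** The rule closes the Intervention section: "Participants will only be discontinued from the study in the case of the training being assessed as unsafe by study personnel with medical background". What ends is participation in the study, and the trigger is a judgement about the training.

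Under Study design, the two arms are "usual care plus a 12-week exercise program or a usual care-only control arm", so the programme is given in one arm only. Of the controls, the Control group section says: "They will undergo all study measurements at the defined timepoints, similar to the intervention group". No discontinuation rule is given for them.

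Two sets of results depend on who is still measured at T3:

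- Feasibility outcomes gives the definition "Retention, defined as the percentage of consenting participants in the intervention and control group completing T3". Table 1 under Progression criteria marks retention as a fundamental objective: red below 65%, amber from 65% to 80%, green from 80%.
- The Statistical analysis plan section says: "Effects will be analyzed at T3 (post-intervention), and further analysis will be made to see if these effects sustain until T4". Results are means, standard deviations and standardized mean differences, without formal tests.

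The article nowhere separates stopping the training from leaving follow-up. The precautions against missing data named under Strengths and limitations are reminders, which cannot bring back someone removed by rule.

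**The concern.** Stopping an intervention and ending follow-up are different events, and this sentence merges them. Staff who follow it literally would stop measuring a participant because the exercise was judged unsafe for her. A control in the same state of health would have no training to be judged and would stay in the measurement schedule.

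Two things are at stake. First, the loss is tied to one arm and probably to health, so the exercise-arm participants still measured at T3 and T4 may look better than the whole arm would have looked. Second, a safety stop is booked as a failure to complete T3, although the participant might well have attended T3 if invited. Retention is one of the criteria that decide whether and how a definitive trial goes ahead, so it matters whether a low figure means that people left or that the protocol removed them.

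**Working it through.** **Inputs.** N = 21, planned as 14 and 7 (Sample size: "Our 2:1 randomization design (14 interventions, 7 controls"). Retention thresholds are those of Table 1. The document gives no expected number of unsafe assessments, so a range is shown.

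**The plan's own retention figure.** Sample size states a 95% interval of 62 to 98% for 80% retention with N = 21. The standard error is √(0.80 × 0.20 / 21) = 0.0873. With t(0.975, 20 df) = 2.086, the interval is 0.80 ± 0.182, or 61.8% to 98.2%. The stated figure reproduces and is not in dispute.

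**Which arm can meet the trigger.** The training exists in the exercise arm only, so the rule can remove up to 14 of 14 planned exercise participants and 0 of 7 controls.

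**Cost to retention.** Each removal before T3 costs 1/21 = 4.8 points pooled and 1/14 = 7.1 points in the exercise arm. With k removals and no other loss:

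| k | Pooled, (21 − k)/21 | Exercise arm, (14 − k)/14 | Control arm |
|---|---|---|---|
| 1 | 95.2% | 92.9% | 100% |
| 2 | 90.5% | 85.7% | 100% |
| 3 | 85.7% | 78.6% | 100% |
| 4 | 81.0% | 71.4% | 100% |
| 5 | 76.2% | 64.3% | 100% |

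Green needs 0.80 × 21 = 16.8, so at least 17 completers. Four losses leave 17/21 = 81.0%, still green; the fifth, from any cause, gives 16/21 = 76.2%, amber. If three participants are lost for other reasons (18/21 = 85.7%), one safety removal leaves 17/21, green, and a second leaves 16/21, amber. Table 1 has a single retention line, read here as pooled.

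**Cost to the effect estimates.** Suppose, purely for illustration, that 2 of 14 are removed and their unseen T3 values would lie 1 SD worse than the mean m of the other 12. The full-arm mean is (12m + 2(m − 1 SD))/14 = m − 2/14 SD, so the observed mean is flattered by 2/14 = 0.14 SD. Neither input comes from the document.

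**Scale for comparison.** With 14 against 7, the standard error of a difference in means is about √(1/14 + 1/7) = 0.46 SD. The illustrated shift is 0.14/0.46 = 0.30 of that.

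**With follow-up kept open.** The rule itself costs 0 of 14 exercise-arm outcomes. Only losses through withdrawal, illness or death remain, and these can occur in either arm.

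**The case against.** The best defence is that the wording is loose. The sentence ends a description of the training, its trigger is the training, and it may simply mean leaving the programme. A journal article condenses a fuller protocol, which may deal with follow-up after stopping. The word only is also protective, since poor attendance or disease progression is then no ground for removal. This lowers confidence about intent. It does not change what the published rule says, and if the intent was training only, the correction is harmless and still needed.

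The effect is also small. Eligibility requires ECOG 0–1 and excludes conditions that make participation unsafe, so removals may be few. Four alone leave pooled retention green. No tests are planned, the feasibility judgement is holistic, and the illustrated shift is well inside sampling error. All of this stands and limits the severity.

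Three stronger readings are tempting, and the document does not support them:

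- A reader might infer that retention ceases to measure willingness to stay. It is defined as completing T3; willingness is not part of the definition, and counting a safety removal as a failure is conservative for feasibility.
- A reader might infer a comparison of exercise survivors with every control. Controls can also withdraw, progress or die. Only the loss caused by this rule is one-sided.
- A reader might infer that harms go unrecorded. Adverse events related to study procedures are collected continuously and graded with an exercise-specific method, so an event of that kind that led to removal would normally be captured. What is lost is later scheduled measurement.

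**Conclusion.** The concern holds as a fault in a stated rule. As written, an unsafe assessment takes an exercise-arm participant out of the T3 and T4 measurements, and out of T2 if it falls before week 6, with no counterpart among controls.

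The arithmetic on retention is firm given the planned 14/7 split, which simple randomization need not deliver exactly. The direction of bias in the effect estimates rests on an inference: participants judged unsafe to train are probably in worse health than the rest. That is plausible, but the document does not establish it. The 0.14 SD shift is an illustration and not an estimate.

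Because the analysis is descriptive, the damage is to effect sizes and to the meaning of a fundamental progression criterion; no error rate is affected. The point merits correction at moderate priority.

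**What to change.** Reword the sentence so that an unsafe assessment ends the training and not study follow-up. State that these participants:

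- are still invited to the remaining scheduled assessments that the responsible staff consider suitable for them, unless they withdraw consent;
- stay in the arm to which they were randomised when results are summarised.

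Report the number who stop training for safety, by timing, separately from retention, so that the steering committee can tell the two apart. If anyone has already been removed under the current wording, report that number and show retention with it identified.

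None of this alters when training is stopped or who decides.

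The cost is a sentence or two, a few visits already in the schedule, and possibly a formal amendment with ethics approval under Modification of the protocol. With 19 of 21 participants already included according to Trial status, the gain is limited to follow-up still to come, clearer reporting, and the wording carried into the definitive trial.
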